#### Tumor imaging at the end of treatment and during the follow-up

2.7.3

For subjects who complete treatment or discontinue treatment for reasons other than disease progression, the tumor imaging assessment should be performed. Subsequent imaging assessments should continue at the protocol-specified time points until one of the following occurs: initiation of a new anti-cancer therapy, objective disease progression, death, or study completion, whichever comes first.

### Toxicity monitoring and dose modification

2.8

Each subject will be assessed for adverse events (AEs) during the study or follow-up, which will be graded and documented according to National Cancer Institute General Terminology for Adverse Events (NCI-CTCAE), version 5.0. All AEs of unknown etiology occurring during the treatment should be evaluated for treatment-related AEs. An AE is defined as any adverse medical event that occurs in a clinical research subject from the time of signing the informed consent form, whether or not causally related to the study drug. A serious adverse event (SAE) is defined as an adverse medical event that meets at least one of the following criteria:1) Deaths, excluding deaths due to disease progression for study indications; 2) Life-threatening, meaning that the subject is at risk of death when this AE occurs; 3) Hospitalization or extended hospitalization; 4) Permanent or severe disability/incapacity; 5) Congenital anomalies/birth defects; 6) Other significant medical events, defined as events that jeopardize the subject or require medical intervention to prevent any of the above.

Dose-limiting toxicities are defined as Grade ≥4 hematologic toxicities, Grade ≥3 non-hematologic toxicities, and any toxicity requiring discontinuation of either fruquintinib or sintilimab for ≥21 days. Before each treatment cycle, toxicity will be assessed through patient history, physical examination, and laboratory evaluations (including complete blood count, blood biochemistry, coagulation, thyroid function, urinalysis, serum tumor markers). Notably, for subjects whose ALT or AST increases by >3× ULN, or increases by >2× baseline level, blood biochemistry tests should be performed per institutional standard practice (8). For subjects with normal baseline ALT, AST, or total bilirubin (TBIL), grade 2 elevations of AST, ALT (3–5 × ULN), or TBIL (1.5–3 × ULN); and for subjects with baseline ALT, AST, or TBIL > ULN, elevations of AST, ALT, or TBIL of ≥50% from baseline (meeting grade 2 criteria) with a duration of <7 days: dosing should be interrupted until the event improves to grade 0–1 or baseline level, after which dosing may be resumed. For subjects with normal baseline ALT, AST, or TBIL, grade 3 or 4 elevations of AST, ALT (>5 × ULN), or TBIL (>3 × ULN); and for subjects with baseline ALT, AST, or TBIL > ULN, elevations of AST, ALT, or TBIL of ≥50% from baseline (meeting grade 3 or 4 criteria) with a duration of ≥7 days: permanent discontinuation of the study drug is required.

For AEs related to fruquintinib, the dose of fruquintinib will be reduced to 3 mg/day for Grade ≥3 toxicity, and further reduced to 2 mg/day if necessary (8, 23). After AEs resolve to Grade 0–1 or to baseline levels, drug administration as scheduled will be resumed. Close monitoring for proteinuria and hypertension will be performed per protocol throughout the study. Importantly, for proteinuria of grade 2 or higher (≥2g/24h), fruquintinib will be temporarily withheld until the level decreases to <1g/24h, after which treatment can be resumed at a reduced dose. Permanent discontinuation will be required in cases of nephrotic syndrome or if proteinuria does not recover to <1g/24h. Hypertension will be managed according to American Heart Association guideline. Grade 3 hypertension will necessitate treatment interruption; upon recovery to grade 1, therapy can be restarted at a lower dose. Any grade 4 hypertension will result in permanent treatment discontinuation. Dose adjustments of sintilimab are not permitted in this trial. To manage intolerable AEs, sintilimab administration will be withheld until toxicity recovers to Grade 0–1 or to baseline levels. The maximum permitted interruption of sintilimab due to corticosteroid use for managing immune-related adverse events will not exceed 12 weeks.

Investigators must ensure that patients receive the prescribed radiation dose as defined in the protocol. If a treatment-related adverse event (TRAE) necessitates an interruption of radiotherapy, the pause should not exceed two weeks. If an interruption extends beyond two weeks due to TRAE, the decision to resume radiotherapy must be made following careful evaluation by investigators. In such cases, the patient’s treatment plan will be considered a major protocol deviation, and the patient will be regarded as a dropout. If radiotherapy is interrupted due to TRAE, administration of the study drug should be suspended concurrently. To facilitate treatment completion, appropriate prophylactic measures and supportive nutritional care are recommended. Treatment may resume once the AE recovers to CTCAE Grade 2 or lower.

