### Interventions

2.5

The study flow is presented in **Figure 1**. Patients in the intervention group will be given sintilimab (200 mg, IV, D1, once every 3 weeks) plus fruquintinib (5 mg, po, D1-14, once every 3 weeks) in combination with liver-directed radiotherapy. A 21-day treatment cycle of sintilimab (200 mg, IV, D1, once every 3 weeks) will be given intravenously on day 1 of each cycle, and fruquintinib will be given on days 1 through 14 of each cycle. The radiologist will determine the radiation division pattern based on the location and volume of the liver metastases. For liver oligometastases, stereotactic body radiation therapy (SBRT) will be performed with a dose of 40–50 Gy/5 F, 60–70 Gy/10 F, or 65 Gy/13 F. For multiple liver metastases, SBRT plus low-dose radiation therapy (LDRT) will be performed. The appropriate lesions will be selected to receive SBRT with a dose of 40–50 Gy/5 F, 60–70 Gy/10 F, or 65 Gy/13 F, and the remaining liver lesions will undergo LDRT at a total dose of 1–10 Gy with 0.5-2.0 Gy/F. One or more appropriate lesions will be selected by the physician based on the surrounding organs at risk. Extrahepatic lesions will not receive radiation therapy. Liver radiotherapy will be administered within 1 week of initiating immunotherapy. For patients receiving a 5-fraction regimen, the volume receiving ≥15 Gy will be limited to <700 cc and the Dmean will be <16 Gy. For those treated with 10 or 13 fractions, the volume receiving ≥24 Gy will be limited to <700 cc and Dmean will be <24 Gy for patients with Child-Pugh class A, and the limits will be V18Gy <700 cc and Dmean <18 Gy for patients with Child-Pugh class B. **Figure 2** shows an example of target area delineation and radiation dose distribution for two patients.

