**Figure 2 f2:**
[figure not shown]
An example of target area delineation and radiation dose distribution for two patients. The top row **(A–C)** represents a patient with liver oligometastasis receiving 40 Gy/10 F irradiation, with the images displayed in axial, coronal, and sagittal planes. The bottom row **(D–F)** represents a patient with multiple liver metastases receiving 10 Gy/5 F irradiation, with the images displayed in axial, coronal, and sagittal planes.

Patients in the control group will be treated with sintilimab plus fruquintinib. A 21-day treatment cycle of sintilimab (200 mg) will be given intravenously on day 1 of each cycle, and a 21-day treatment cycle of fruquintinib (5 mg) will be given orally on days 1 through 14 of each cycle. Patients in the standardized treatment group will be treated with fruquintinib (5 mg) only, and a 21-day treatment cycle of fruquintinib will be given on days 1 through 14 of each cycle.

For all included patients, CT scans will be repeated every 12 weeks during the treatment to evaluate the efficacy, and the regimen will be continued if the response is evaluated as complete response (CR), partial response (PR), stable disease (SD), or non-progressive disease (PD). Sintilimab is administered for no more than 2 years. No dose adjustments of sintilimab are permitted throughout the study. Fruquintinib is continued until toxicity is intolerable, PD, or death.

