#### Statistical analysis methods

2.13.2

Clinical characteristics and safety outcomes will be summarized using descriptive statistics. Unless otherwise stated, continuous data will be statistically described using mean (± standard deviation) or median (minimum, maximum). Categorical data will be statistically described using frequencies (percentages). Cox proportional hazard models will be used for univariate and multivariate survival analyses, with HRs and 95% confidence intervals (CIs) calculated. Subgroup analyses will be conducted by the characteristics of patients and liver metastases (liver oligometastases or multiple liver metastases). Both the intention-to-treat (ITT) population and the per-protocol population will be used for efficacy and safety analyses. The worst-case imputation and complete-case analysis will be performed as sensitivity analyses to handle the missing data and dropouts (24). The SAS 9.2 (or higher) will be used for statistical analyses, using a one-sided 0.05 hypothesis test of superiority, and 95% CIs and *P* values will be reported for group comparisons.

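### Calling a patient a 'dropout' after a toxicity-driven radiotherapy pause of over two weeks can happen only in the intervention arm and invites one-sided exclusion or imputation

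*Protocol article*

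**What the plan says.** Section 2.8 (Toxicity monitoring and dose modification) covers radiotherapy pauses caused by treatment-related adverse events. For a pause of more than two weeks it first says: "If an interruption extends beyond two weeks due to TRAE, the decision to resume radiotherapy must be made following careful evaluation by investigators". The next sentence says that the patient's treatment plan "will be considered a major protocol deviation, and the patient will be regarded as a dropout".

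Section 2.5 (Interventions) gives radiotherapy to the intervention arm alone; that arm receives the two drugs "in combination with liver-directed radiotherapy. A 21-day treatment cycle of sintilimab" and so on. For the comparator: "Patients in the control group will be treated with sintilimab plus fruquintinib". Section 2.13.1 makes intervention versus control the primary analysis.

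Section 2.13.2 contains two relevant statements. On populations: "Both the intention-to-treat (ITT) population and the per-protocol population will be used for efficacy and safety analyses". On dropouts: "The worst-case imputation and complete-case analysis will be performed as sensitivity analyses to handle the missing data and dropouts".

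Two sections continue follow-up. Section 2.7.3 continues scheduled imaging after treatment stops without progression, "until one of the following occurs: initiation of a new anti-cancer therapy, objective disease progression, death, or study completion". Section 2.12 continues to collect adverse events and survival status after withdrawal, and applies the scheduled procedures to those who can still be followed.

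**The concern.** Radiotherapy is what differs between the two arms of the primary comparison. A toxicity-driven interruption of it is a post-randomisation consequence of treatment, not a missing outcome. Calling such a patient a dropout merges two different things: departing from the planned treatment and leaving the study.

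The word matters because section 2.13.2 attaches analysis methods to it. A major deviation would ordinarily leave the per-protocol set, and a dropout may be taken out of a complete-case analysis. Both losses would be related to toxicity and confined to the radiotherapy arm. If the affected patients have a worse prognosis, the comparison tilts towards radiotherapy. Worst-case imputation, if it counts the same patients as failures, tilts the other way. The spread between the two analyses would then partly reflect a label and not real missing data.

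Drug interruptions have no matching rule. For sintilimab the same section says "The maximum permitted interruption of sintilimab due to corticosteroid use for managing immune-related adverse events will not exceed 12 weeks", and no drug pause in any arm is said to make the patient a dropout.

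**Working it through.** **1. Who can be affected.** The trigger is a radiotherapy interruption. Radiotherapy is given only in the intervention arm (section 2.5), so the number of control patients who can meet the rule is zero by design.

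**2. Do the passages agree?**
- Section 2.8, first sentence: after more than two weeks, resuming radiotherapy is still open. Next sentence: the patient is a dropout. A patient could be back on radiotherapy and a dropout at once.
- Sections 2.7.3 and 2.12: imaging, adverse events and survival continue to be collected, so PFS and OS can be observed in a patient classed as a dropout.
- Section 2.13.2: dropouts are grouped with missing data. For these patients the data need not be missing.
- 'Dropout' is nowhere defined as leaving follow-up or leaving the analysis.

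**3. The plan's own dropout figure.** Section 2.13.1 assumes 5%, with 24 intervention and 23 control patients. That is 0.05 × 24 = 1.2 patients in the intervention arm, or 0.05 × 47 = 2.35 overall. Two toxicity cases are 2/24 = 8.3% of the arm and three are 3/24 = 12.5%, so two already exceed the allowance for that arm.

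**4. Size if these patients were deleted.** The article gives neither an interruption rate nor the prognosis of interrupted patients. Both are assumptions here.

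Inputs from section 2.13.1: 24 versus 23 patients, control median 1.8 months, 18 months' accrual, 12 months' follow-up, one-sided 0.05. Further assumptions: exponential PFS, uniform accrual and no true effect. A share q of patients in both arms has 1, 2 or 3 times the hazard of the rest, and these patients are removed from the intervention arm only. The test is the log-rank Z = (O − E)/√V, rejecting at Z < −1.645. The apparent HR is exp of the mean of (O − E)/V. There were 8,000 runs per cell, so the Monte Carlo standard error near 6% is √(0.06 × 0.94/8000) ≈ 0.3 percentage points.

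| Hazard multiple | q | All kept: error (HR) | Deleted: error (HR) | Censored at 1 month: error (HR) |
|---|---|---|---|---|
| 1 | 5% | 5.5% (1.00) | 5.4% (1.00) | 5.7% (1.00) |
| 1 | 10% | 5.6% (1.00) | 5.3% (1.00) | 5.8% (1.00) |
| 1 | 20% | 4.9% (1.00) | 5.6% (1.00) | 5.2% (1.01) |
| 2 | 5% | 5.7% (1.00) | 7.1% (0.97) | 5.8% (0.99) |
| 2 | 10% | 5.8% (1.00) | 7.0% (0.95) | 6.4% (0.98) |
| 2 | 20% | 5.4% (1.00) | 10.1% (0.90) | 6.8% (0.96) |
| 3 | 5% | 5.3% (1.00) | 6.8% (0.97) | 6.3% (0.99) |
| 3 | 10% | 5.3% (1.00) | 8.8% (0.93) | 6.1% (0.98) |
| 3 | 20% | 6.1% (0.99) | 12.7% (0.86) | 7.1% (0.96) |

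**5. Cross-check by formula.** With about 45 events (47 × 0.95 = 44.65), type I error ≈ Φ(−ln(HR) × √45/2 − 1.645). Large-sample apparent HRs under deletion are 0.963 and 0.942 at 10% removed (2 and 3 times the hazard), and 0.910 and 0.849 at 20%. For HR 0.910: 0.0943 × 3.354 = 0.316, and Φ(0.316 − 1.645) = Φ(−1.329) ≈ 9.2%. For HR 0.849: 0.1637 × 3.354 = 0.549, and Φ(−1.096) ≈ 13.7%. At 10% removed the formula gives about 6.4% and 7.4%. These agree broadly with the table.

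**The case against.** The best defence is that the article plans an ITT analysis and nothing in it excludes these patients from that analysis. The complete-case and worst-case methods are described as sensitivity analyses only. A per-protocol set that leaves out major deviations is normal when reported beside ITT. Because follow-up continues, an interrupted patient with observed PFS would usually stay in a complete-case analysis and would need no imputation. The neighbouring sentence on resuming radiotherapy suggests that 'dropout' may describe treatment and not the dataset. All of this stands, and it limits the point to the label and what the label may trigger.

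The size can also be challenged. The 10-20% rates and the 2 to 3 times hazards have no source in the article, and the deletion column assumes removal from the analysis that decides the trial. At the article's own 5% dropout figure the error is about 7%, and with censoring at one month in place of deletion it is mostly 6-7% even at the higher rates. That stands too.

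The defence does not remove two things. The article never says that 'dropout' is only a treatment label, while section 2.13.2 uses the same word for an analysis problem. And neither ITT nor per-protocol is named as primary in this article, so a reader cannot tell that the ITT result decides.

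A reader might also blame section 2.7.3 for ending imaging when a new therapy starts. That rule applies to every arm. How PFS is censored is a matter for the choice of estimand or for an analysis plan that is not shown, so it is no part of this point.

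**Conclusion.** The point holds in limited form. The article has an explicit rule, triggered by toxicity and possible only in the intervention arm, that gives patients with observable outcomes a label tied to missing-data methods. It is not reconciled with the sentence before it or with sections 2.7.3, 2.12 and 2.13.2.

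A reader might infer that poorly tolerating patients will be removed and the randomised comparison lost. The documents do not support that, since ITT is planned and follow-up continues. The harm arises in the per-protocol and complete-case analyses, and in ITT only if 'dropout' is taken to end follow-up or to trigger censoring or imputation.

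The error rates of about 7% (5% removed), 7-9% (10%) and 10-13% (20%) are conditional on outright deletion and on a hazard 2 to 3 times that of other patients. They compare with about 5-6% when everyone is kept. Bias vanishes if interruption is unrelated to prognosis, and its direction reverses if the patients are imputed as failures.

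**What to change.** - In section 2.8, delete the words that class the patient as a dropout, and record the interruption as a protocol deviation only.
- State that such patients stay in scheduled follow-up and in the ITT analyses of PFS and OS with their observed data.
- In section 2.13.2, reserve 'dropout', and the missing-data sensitivity analyses, for withdrawal of consent or loss of contact.
- Name ITT as the primary efficacy population and per-protocol as supportive.
- Reconcile the section 2.8 sentences on resuming radiotherapy and on dropout. This concerns classification and analysis only; the clinical rule on pausing or resuming radiotherapy is not in question here.

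The cost is protocol wording. Sections 2.7.3 and 2.12 already provide for the imaging and follow-up, so no patients are added and few if any scans. Because the trial is open-label, the change is best made before outcomes are known.

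### Section 2.8 sets a Grade 2 restart threshold after a radiotherapy interruption without saying whether it covers the suspended drugs, whose own restart and stopping rules are stricter

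*Protocol article*

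**What the plan says.** All the relevant rules are in the protocol article, section 2.8 (Toxicity monitoring and dose modification).

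- **Radiotherapy paragraph.** It couples the drugs to the radiotherapy pause: "If radiotherapy is interrupted due to TRAE, administration of the study drug should be suspended concurrently". It closes with its only graded restart condition: "Treatment may resume once the AE recovers to CTCAE Grade 2 or lower".
- **Fruquintinib.** The dose rule is "For AEs related to fruquintinib, the dose of fruquintinib will be reduced to 3 mg/day for Grade ≥3 toxicity", and the restart rule that follows is "After AEs resolve to Grade 0–1 or to baseline levels, drug administration as scheduled will be resumed".
- **Sintilimab.** "To manage intolerable AEs, sintilimab administration will be withheld until toxicity recovers to Grade 0–1 or to baseline levels".
- **Liver tests.** The hepatic rule comes earlier in the section and is not tied to any cause. With normal baseline values, a grade 2 rise (ALT or AST 3–5 × ULN, bilirubin 1.5–3 × ULN) means dosing is held until grade 0–1 or baseline. A grade 3 or 4 rise (ALT or AST above 5 × ULN, bilirubin above 3 × ULN) means the study drug is permanently stopped.

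**The concern.** The closing sentence of the radiotherapy paragraph follows an instruction that has stopped both radiotherapy and the drugs, and its subject is the undefined word *Treatment*. Elsewhere the paragraph names radiotherapy when it means radiotherapy. In the paragraph just before it, the word is used three times for something resumed, interrupted or discontinued, and each time it means drug: "fruquintinib will be temporarily withheld until the level decreases to <1g/24h, after which treatment can be resumed at a reduced dose", "Grade 3 hypertension will necessitate treatment interruption; upon recovery to grade 1, therapy can be restarted at a lower dose" and "Any grade 4 hypertension will result in permanent treatment discontinuation". A site could reasonably conclude that Grade 2 is enough to restart fruquintinib and sintilimab as well.

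At stake is hepatic safety handling in the arm whose liver is irradiated, and consistent drug exposure within that arm. Two sites with the same patient could act differently: one restarts both drugs, while the other holds them or stops them for good. Both could point to section 2.8.

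**Working it through.** No power or sample-size formula bears on this point. The check compares the stated rules, with one proportion for the exposed share.

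**Step 1. Thresholds side by side (all from section 2.8).**

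| Situation | Drug rule | Closing sentence, if it covers drugs |
|---|---|---|
| Grade 2 ALT/AST/bilirubin, normal baseline | Hold until grade 0–1 or baseline | Restart allowed at Grade ≤2 |
| Grade 3–4 ALT/AST/bilirubin, normal baseline | Permanent stop | Restart allowed once at Grade ≤2 |
| AE related to fruquintinib | Restart at Grade 0–1 or baseline | Restart allowed at Grade ≤2 |
| Intolerable AE on sintilimab | Withhold until Grade 0–1 or baseline | Restart allowed at Grade ≤2 |
| AE covered by no drug-specific rule | None stated | Restart allowed at Grade ≤2; no conflict |

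**Step 2. Two hepatic cases in a normal-baseline patient whose radiotherapy is paused for a liver TRAE.**

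- *ALT peaks at grade 2.* The Grade ≤2 condition is already met when the pause begins. The hepatic rule still requires a hold until grade 0–1 or baseline. The two thresholds differ by one grade.
- *ALT peaks at grade 3 and falls back to 3–5 × ULN.* The Grade ≤2 condition is now met. The hepatic rule does not merely hold the drug here; it has already required permanent discontinuation. The choice is between restarting and never restarting.

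**Step 3. How far attribution limits the conflict.** The fruquintinib rule covers AEs related to that drug, and the sintilimab rule covers intolerable AEs. An event attributed only to radiation may fall outside both. The hepatic rule carries no such limit, so attributing a liver event to radiotherapy does not avoid it. That is why it is the main conflict.

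**Step 4. The radiotherapy-only reading.** If *Treatment* means radiotherapy alone, there is no conflict. But the paragraph has suspended the drugs and then gives them no restart condition. For an event under none of the drug-specific rules, the article does not say when the drugs come back.

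**Step 5. Exposed share.** Section 2.13.1 plans 24 + 23 + 15 = 62 patients, and only the 24 in the intervention group receive radiotherapy: 24 / 62 = 38.7%. This is the size of the arm in which the sentence can operate, not a count of affected patients. The article gives no expected rate of radiotherapy interruption or of liver TRAEs.

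**The case against.** The strongest reply is that the sentence means radiotherapy. It sits in a paragraph that opens with delivering the prescribed radiation dose. The sentence just before it speaks of completing treatment, which fits a fixed radiation course better than fruquintinib, which has no planned end. This has real weight, and a reader should not infer that the protocol plainly orders drug restart at Grade 2. The text supports an unresolved ambiguity, not a definite contradiction. The ambiguity remains because the same paragraph has just suspended the drugs and nothing elsewhere limits the sentence.

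A second reply is that the sentence only permits, while the drug rules direct, so a careful site would satisfy both and let the specific rule govern. This also lowers the severity. It relies on a precedence rule that the article does not state.

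A third reply is that a journal article condenses the full protocol. That would answer a complaint about missing detail. Here every threshold is printed, and the difficulty is how the printed rules fit together.

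The proteinuria and hypertension rules are also stricter than Grade 2, but nothing shows that liver radiotherapy is likely to be interrupted for either. They serve above only as evidence of how the word is used.

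**Conclusion.** The point holds as a minor safety-consistency correction. On a plausible reading, the closing sentence of section 2.8 allows both drugs to restart at a grade where the hepatic rule holds them, or after an event for which that rule stops them permanently. Where they apply, it also undercuts the fruquintinib-related and sintilimab restart rules. A TRAE under no drug-specific rule produces no conflict.

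Two assumptions matter. First, the 7-day duration wording in the hepatic rule is taken to qualify only patients with raised baseline values, so that the normal-baseline rules apply regardless of duration. Second, the one-grade difference presumes that the patient's own baseline is not already grade 2.

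A reader might infer that 39% of patients are affected, or that the primary PFS comparison is compromised. Neither is supported. The 39% is the whole intervention arm, the number of affected patients is unknown, and nothing here alters sample size, alpha or the PFS analysis.

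**What to change.** Replace the last sentence of section 2.8 with wording such as:

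> Radiotherapy may be restarted when the AE is at CTCAE Grade 2 or below. Fruquintinib and sintilimab are restarted only when their own criteria in this section are met and no permanent-discontinuation rule in this section applies. Where no drug-specific rule applies, they may be restarted together with radiotherapy.

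The clause on permanent discontinuation is needed. Without it, the new text could be read as allowing restart after a grade 3–4 liver-test rise in a normal-baseline patient, grade 4 hypertension or nephrotic syndrome. The last clause fills the gap that the radiotherapy-only reading leaves.

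The cost is a short wording change and possibly slightly longer drug holds in a few patients. Endpoints, sample size and analysis stay as they are.

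### The restart rule after a radiotherapy interruption does not say whether it covers the study drugs; if it does, it conflicts with the liver-toxicity rules in the same section

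*Protocol article*

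**What the plan says.** All the rules are in section 2.8 (Toxicity monitoring and dose modification) of the protocol article.

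- **Radiotherapy interruption.** "If radiotherapy is interrupted due to TRAE, administration of the study drug should be suspended concurrently". After one sentence on prophylaxis and nutrition, the paragraph ends: "Treatment may resume once the AE recovers to CTCAE Grade 2 or lower".
- **Liver, lower tier.** For grade 2 AST, ALT or total bilirubin elevations with normal baseline values (raised baselines are worded separately), "dosing should be interrupted until the event improves to grade 0–1 or baseline level, after which dosing may be resumed".
- **Liver, upper tier.** For grade 3 or 4 elevations, "permanent discontinuation of the study drug is required".
- **Fruquintinib.** In the text on fruquintinib-related events: "After AEs resolve to Grade 0–1 or to baseline levels, drug administration as scheduled will be resumed". Proteinuria of grade 2 or higher has its own rule: "fruquintinib will be temporarily withheld until the level decreases to <1g/24h".
- **Sintilimab.** For intolerable events, "sintilimab administration will be withheld until toxicity recovers to Grade 0–1 or to baseline levels".

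Section 2.5 gives radiotherapy to the intervention group only. Section 2.13.1 makes intervention versus control the primary analysis. Nothing in the article ranks these rules.

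**The concern.** The radiotherapy paragraph stops radiotherapy and drugs together and then gives one restart criterion for something it calls treatment. An investigator can reasonably take that criterion to release everything the paragraph suspended. On that reading, a patient with a current grade 2 liver abnormality may be re-dosed under one sentence, while another sentence of the same section holds or permanently stops the drug.

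Two things are at stake. The first is patient safety and consistency between sites, because two investigators following the same text could manage identical patients differently. The second is the comparison itself. The control arm gets the same two drugs but can never reach the radiotherapy rule. Drug exposure, and the adverse events that follow from it, could therefore differ between arms partly because of the restart rule. The trial is open-label (section 2.4), so the investigators who apply the rule know the arm.

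**Working it through.** The article gives no figure to reproduce, and the point depends on no sample size or power calculation. The check sets the rules side by side.

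**Step 1. Suppose treatment includes the drugs.** The cases below assume normal baseline values, so that grade 2 is not the patient's baseline.

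| Case | Radiotherapy paragraph | Other rule in section 2.8 | Result |
|---|---|---|---|
| A. Radiotherapy and drugs stopped for a liver event; values at grade 2 | Drugs may restart | Dosing held until grade 0–1 or baseline | Conflict |
| B. Liver elevation reached grade 3–4, now down to grade 2 | Drugs may restart | Study drug permanently discontinued | Conflict, the sharpest |
| C. Fruquintinib-related event, now grade 2 | Drugs may restart | Fruquintinib resumes at grade 0–1 or baseline | Conflict for fruquintinib |
| D. Intolerable event managed by withholding sintilimab, now grade 2 | Drugs may restart | Sintilimab withheld until grade 0–1 or baseline | Conflict for sintilimab |
| E. Purely radiation-related, non-liver event, now grade 2 | Drugs may restart | Neither drug rule clearly applies | No conflict shown |

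Two details of wording bear on A and B.

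- The radiotherapy sentence speaks of an event that recovers to grade 2 or lower, which suggests a fall from a higher grade. For a liver event that means case B. Case A also arises if an event that never exceeded grade 2 is taken to satisfy the criterion.
- The liver rules carry duration limits (under 7 days in the lower tier, 7 days or more in the upper). As punctuated, these attach to patients with raised baseline values. If they were meant for all patients, A and B would hold only for elevations within those durations.

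**Step 2. Suppose treatment means radiotherapy only.** Radiotherapy may then restart at grade 2 while each drug follows its own rule, and A to D no longer conflict. In case E, however, the drugs have been suspended and no sentence clearly says when they restart. The text also does not say whether radiotherapy may proceed while the drugs remain held.

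**Step 3. Which reading does the text support?** Neither securely. The same paragraph names radiotherapy explicitly when it discusses resuming it after a pause of more than two weeks, so the change to a general word may be deliberate. The proteinuria rule uses the same general word for fruquintinib. Against that, the paragraph as a whole is about delivering the prescribed radiation dose.

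**Step 4. Who can be affected?** Only patients in the intervention arm whose radiotherapy is interrupted by a treatment-related event, and only if the event also falls under a stricter rule. The article gives no rate for either condition.

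**The case against.** The strongest reply is that a consistent reading exists. The sentence closes a paragraph about radiotherapy, the general word can mean whichever therapy is under discussion, and the drug rules can run alongside it. The sentence is also permissive, whereas the liver rules are directive and specific to the event, so a careful reader might let the liver rules prevail. This has force: it makes the point a conditional conflict caused by an undefined word, and not a proven contradiction. It does not remove the problem, because the drugs are suspended by that same paragraph and no order of precedence is stated.

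A second reply is that the drug rules have limits. That stands. A reader might infer that both drugs must always be held to grade 0–1, so that the radiotherapy rule contradicts them across the board. The text does not support this. The fruquintinib rule is framed for fruquintinib-related events and the sintilimab rule for intolerable events, and both accept return to baseline. The conflict is firmest for the liver rules, which have no limit by cause.

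A third reply is that an article condenses the full protocol. That would answer a complaint about missing detail. Here the competing rules are all printed in one section. The full protocol may already settle the matter, in which case the article's wording should follow it.

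**Conclusion.** The point holds in conditional form. If the radiotherapy restart sentence covers the drugs, it conflicts with both tiers of the liver rule. The clearest case is a grade 3–4 elevation that has fallen to grade 2: one sentence permits restart, the other requires permanent discontinuation. It may also conflict with the fruquintinib and sintilimab restart rules for the events within their scope. If the sentence covers radiotherapy only, those conflicts disappear, but restart of the suspended drugs is unclear for purely radiation-related events.

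The size cannot be stated as a number of patients or as a bias. A reader might take the planned intervention arm, 24 of the 24 + 23 = 47 patients in the primary comparison (24/47 = 51%), as the extent of the problem. That is only the arm's share, and the affected group is an unknown subset of it. Nor does the article say that liver toxicity will be the commonest cause of interruption; that is a plausible inference, given that the liver is irradiated.

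A radiotherapy-interruption rule that exists in one arm only is inherent in the design and is not itself a fault. What needs resolving is whether it also changes how the shared drugs are restarted. Because the ambiguity concerns re-dosing of patients with current toxicity and is cheap to remove, it should be settled.

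**What to change.** Reconcile the radiotherapy paragraph of section 2.8 with the liver and drug-specific rules in the same section:

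1. State whether the restart sentence applies to radiotherapy, to the drugs or to both.
2. State which rule prevails when the radiotherapy-interruption rule applies together with the liver rules or a drug-specific rule (including proteinuria and hypertension).
3. If drug restart is intended to differ between the intervention and control arms, say so.

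The clinical leads decide the thresholds; this review takes no view on them. The cost is a wording amendment and a site memo.
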